#### Adherence

Patients’ adherence to the study protocol will be ensured through the following measures: (i) During the patients’ weekly therapy sessions, adherence to the study protocol will be discussed alongside their regular progress reviews, including homework completion. Since the study data (e.g., homework completion rates, symptom tracking) are directly informative for the therapist’s clinical planning, this discussion naturally aligns with the therapeutic goals. (ii) Therapists will document adherence-related discussions and any protocol deviations in the Adherence Questionnaire, which will be regularly reviewed by the research team.

Treatment fidelity on the part of the therapists will be ensured through several measures: (i) Therapists will complete a structured protocol after each session, and (ii) a supervision session with the PI will be scheduled for every fourth therapy session.

#### Concomitant care

During the trial, concurrent psychotherapy will be prohibited for participants. This is because receiving additional psychotherapy would not only conflict with the study’s treatment protocol but is also contrary to clinical recommendations. If a participant begins concurrent psychotherapy during the trial, this will result in their dropout from the study in order to maintain the integrity of the trial’s outcomes and ensure consistency in the treatment being evaluated.

### Outcomes

#### Primary outcome

The primary outcome of the JAY trial will be patients’ THA. THA will consist of an overall THA score including the quantity and quality of therapy homework. Patients in both treatment arms will be asked to complete homework assignments between the therapy sessions. This will include at least two diary entries and one individually assigned challenge that has to be documented (via the app or on paper, depending on the study group). Patients will complete at least 16 sessions of therapy, and THA can be assessed after 15 sessions. Non-responders will complete a further eight sessions, so that THA can be rated 23 times over 23 weeks.

The quantity of therapy homework will be assessed according to the relative ratio of completed to requested entries that are implemented in the JAY app or the paper-and-pencil sheets between the treatment sessions. The relative ratio will be computed by dividing the number of completed entries by the number of requested entries and will thus range from 0 to 1. The quality of the entries will be assessed by a pool of clinicians based on the app entries or the homework sheets according to a rating system. Criteria of the rating system include (1) content fit, (2) thoroughness, (3) competence of behaviour/thoughts, and (4) clinical relevance. As these quality data might be subjectively biased, they will be further evaluated by five independent clinical raters on a 4-point Likert scale (0 = poor quality, 1 = low quality, 2 = largely good quality, 3 = good quality). The clinical ratings will be conducted based on a rating manual specifying the quality criteria. These aspects do not necessitate any further subjective interpretation by the evaluating clinician, thereby minimizing the potential for bias. Intraclass correlation coefficients (ICC) will be computed to assess the interrater agreement, applying a two-way mixed model for consistency and absolute agreement. In a previous study on the AUTHARK app—the child version of the JAY app—a preliminary analysis of 15 app and paper-and-pencil entries was conducted and interrater reliability for five independent raters was assessed [41]. Consistency for this method was evaluated as “very good” (0.95). The values for absolute agreement ranged between 0.73 (“average”) and 0.87 (“good”) [84]. To calculate the overall THA score, the product of the relative ratio (e.g., 17 completed entries with 30 required entries (17/30 = 0.57) and the average quality score (i.e., from 0 to 3) will be computed. Therefore, the THA score ranges between 0 and 3.

Initially, a descriptive report will be provided for each assessment time point, detailing the quantity of finalized app entries or self-observation sheets, along with the outcomes of the coding process. Subsequently, we will display the change of mean values for each specific aspect over time, both within and across the different groups.

#### Secondary outcomes

Secondary outcomes include:The quantity of therapy homework, as assessed by the relative ratio of completed to requested entries within the JAY app or on the paper-and-pencil sheets between the treatment sessions.Quality of the entries, as rated by a pool of clinicians based on the app entries or the homework sheets according to the rating system mentioned in the previous section.Patient-rated symptoms of anxiety and depression, assessed by the Internalizing Problems scale of the self-report YSR/11-18R [69, 70] as well as the self-report scales for anxiety (SCL-AD-S) and for depression (SCL-DEP-S) from the DISYPS-III [71]. Reliability and validity as well as sensitivity to change of the German version of the YSR/11-18R and the DISYPS-III scales have already been demonstrated in German samples [70, 71]. The Internalizing Problems scale of the YSR/11-18R will be assessed at every measurement time point and the SCL-AD-S and SCL-DEP-S will be assessed at T0 and T3.Caregiver-rated symptoms of anxiety and depression, assessed by the Internalizing Problems scale of the caregiver-report CBCL/6-18R [69, 70] as well as the caregiver-report scales for anxiety (SCL-AD-P) and for depression (SCL-DEP-P) from the DISYPS-III [71]. Reliability and validity as well as sensitivity to change of the German version of the CBCL and the DISYPS-III scales have already been demonstrated in German samples [70, 71]. The Internalizing Problems scale of the CBCL/6-18R will be assessed at every measurement time point, and the SCL-AD-P and SCL-DEP-P will be assessed at T0 and T3.Clinician-rated symptoms of anxiety and depression based on the ILF-INTERNAL from the DISYPS [72], assessed at T0 and T3.Individually defined problem behaviours were rated by the patients using an individual problem list (IPL) in every therapy session. The problem list allows for the assessment of four targeted issues, rated on a 5-point Likert scale, and of the burden of the problems, rated on a 10-point Likert scale. Individual problem lists have been shown to be reliable, valid, and sensitive to change [85].Patient- and caregiver-rated comorbid symptoms and overall behavioural and emotional problems, measured using the remaining scales Externalizing Problems and Total Problems of the self-report YSR/11-18R and the caregiver-report CBCL/6-18R [69, 70]. Reliability and validity as well as sensitivity to change of the German version of these scales have been demonstrated in German samples [70]. These outcomes will be measured at T0 and T3.Patients’ adherence during the weekly therapy sessions (e.g., engagement in tasks and activities) will be measured using the clinician-rated Adherence Questionnaire [68], which will be assessed after every therapy session. This was adapted from the AUTHARK trial [41], in which good internal consistencies were reported.Quality of life, assessed using the Revised Questionnaire for Health-Related Quality of Life Assessment in Children and Adolescents (KINDL^R^) [73], which evaluates aspects related to physical and psychological well-being, the adolescent’s self-worth, as well as friendships and family relationships. Reliability and validity as well as sensitivity to change of scale have been demonstrated in German samples [86, 87]. This outcome will be assessed at T0 and T3. Sense of global self-worth, assessed using a modified German version of the Self-Perception Profile for Children, called the Harter scale [74, 75], which evaluates perceptions of cognitive and physical competence, peer acceptance, physical appearance, and self-worth. Reliability and validity of the original scale were demonstrated in a German clinical sample [88]. This outcome will be assessed at T0 and T3. Emotion regulation strategies were assessed using a modified version of the Questionnaire to Assess Children’s and Adolescents’ Emotion Regulation Strategies (FEEL-KJ) [76], which evaluates adaptive and maladaptive strategies to regulate feelings of anxiety and sadness. Reliability and validity have been demonstrated [76]. This outcome will be assessed at T0 and T3. Retrospective mood assessments will be conducted in every week in which the patient has used the momentary assessment of the JAY app or the paper-and-pencil equivalent. All 16 momentary affective and mental states assessed during the week will be rated retrospectively for the same week on a scale from 0 to 100. Patient-rated satisfaction with the treatment, assessed using a modified version of the self-report Client Satisfaction Questionnaire (ZUF-8-M patient) [77, 78], which has been shown to be reliable, valid, and sensitive to change [89]. Satisfaction will be assessed once, at T3. Patient-rated usability of the JAY app, assessed using a German translation of the System Usability Scale (SUS), which has been shown to be reliable, usable, and valid [90]. The scale measures effectiveness, efficiency, and satisfaction of and with a system. Usability will be assessed for patients in the experimental group once, at T3. Life events in the domains of school, family, and friendships as well as illness, accidents, and losses, as measured by the Zurich Life-Event List (ZLEL), which has been shown to be reliable and valid [91]. This measure will be applied once, at the follow-up (T5) in this study.

### Participant timeline

The participant timeline and measurement schedule for the JAY trial will include four key stages: a screening process, a baseline phase, an intervention period, and a follow-up assessment. The screening process will assess whether families meet the study’s inclusion and exclusion criteria in several steps. First, families will be contacted by telephone for a brief standardized screening. If the initial criteria are met, the patient and a caregiver will be invited for an in-depth screening and information session. Participants who agree to join the study will complete initial questionnaires and undergo three diagnostic sessions to thoroughly assess eligibility (T0). This will be followed by randomization to the experimental or control group. After this, three sessions will be conducted to introduce the patient to their therapist, focusing on building a strong patient-therapist relationship and providing psychoeducation.

The screening process will be followed by a baseline phase that does not include any sessions with the study staff or therapist. Participants will use the JAY app [67] or paper-and-pencil sheets for the purpose of self-observation.

The pre-treatment assessment (T1) will mark the end of the baseline and beginning of the treatment phase. The first part of the treatment phase will involve eight sessions of cognitive-behavioural therapy and up to four sessions with caregivers, followed by an intermediate assessment (T2). The second part of the treatment phase will likewise consist of eight patient sessions and up to four caregiver sessions. Subsequently, another main assessment (T3) will follow. Non-responders to the treatment will be identified using the Internalizing scale from the YSR/11-18R [69] and will continue to receive CBT in a third part of the treatment phase. This will then be followed by a final assessment (T4). Responders to the treatment, as indicated by a lack of significant internalizing symptoms at the main assessment (T3), will conclude their participation in the study. Eight weeks after the final therapy session, they will engage in an initial follow-up assessment (T4).

Finally, every family will complete a follow-up survey (T5) 6 months after T4.

The patient will visit the study site four times for information, screening, and diagnostics, twice for a clinical interview at T3, and 19 (responders) or 27 (non-responders) times for sessions with the therapist. Caregivers will visit the study site for the screening/information session, once for taking the patient’s history, and up to eight times (responders) or 12 times (non-responders) for sessions with the therapist.

Therapy homework adherence, treatment fidelity, and an individual problem list will be assessed every session and a retrospective mood assessment will be conducted every other week. At the main assessment points (T0, T3), internalizing symptoms will be assessed using self- and caregiver-report questionnaires as well as clinical interviews. Comorbid conditions will be assessed only using self- and caregiver-report questionnaires. At the intermediate assessment (T2), internalizing symptoms will be assessed by the patient and the caregiver (see Fig. 5).

**Fig. 5 Fig5:**
[figure not shown]
SPIRIT figure

### Sample size

This study will include *N* = 70 adolescents (35/35) in order to explore the impact of smartphone-augmented CBT on therapy homework adherence among adolescents with depressive and anxiety disorders. Based on a recent systematic review [49], which analyzed the effects of adjunctive apps on therapy across 19 studies, the sample size of 70 in our study lies within the range of reported sample sizes, thus providing a solid basis for comparing the efficacy of adjunctive mobile applications in therapeutic settings. Additionally, a study employing a comparable methodology, which involves a comparison of two groups of 35 participants over four evaluation periods (including before treatment, after treatment, and follow-up assessments), anticipates moderate impacts of their app specifically on therapy homework adherence. For the comparison between groups across four measurement time points, a power analysis indicated a power of 0.84 with a sample size of 35 per group (app vs. no app) at an α level of 0.5 [66]. Additionally, the statistical power of a sample can be enhanced through a large number of observations per participant [34, 92]. In our research, THA will be evaluated for a minimum of three homework tasks per week over approximately 16 weeks.

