## Statistical methods

### Statistical methods for primary and secondary outcomes

#### Analyses of primary endpoint

The primary analysis set adheres to the intention-to-treat (ITT) principle, comprising all patients randomised with a valid baseline assessment. Additionally, per-protocol analyses will involve all patients who attend at least 50% of the planned treatment sessions and provide a valid follow-up. The primary endpoint is the overall THA score across the intervention (sessions 1–16). Subsequent analyses assess changes in phase 1 (sessions 1–8 from T1 to T2) and changes in phase 2 (sessions 9–16, between T2 and T3). A mixed model repeated measures multivariate analysis of variance will be conducted, with the between-subjects factor Group (smartphone-augmented vs. traditional), the within-subjects factor Time (T2, T3), and the interaction effect of Group × Time.

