### Missing data

It is important to minimize treatment discontinuation among patients and ensure that all patients are followed up and documented after treatment discontinuation in order to collect the data according to the intention-to-treat (ITT) principle. Multiple imputation approaches will be employed to evaluate the potential impact of up to 20% attrition, considering proxy measures and assuming specific patterns of missingness not at random. These details will be documented in a statistical analysis plan. Additionally, supporting evidence will be provided by analyzing subjects who are essentially observed and treated per protocol.

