A final aspect to consider concerns the highly effective nature of the control condition [49], which might make it difficult to identify the incremental effect of the app. It is possible that a larger sample will be required to detect significant differences.

Nonetheless, the JAY trial is expected to provide valuable insights into the applicability of a smartphone app used as an adjunct to CBT-based psychotherapy for youth, and into its impact on adherence to therapy homework between sessions. The app’s utility in supporting diagnostics and intervention will be evaluated, as well as its effect on various outcome measures. The results of this study will contribute to preparing research in the growing field of CBT app development and provide a scientific basis for the use of such apps in psychotherapy with adolescents.

Therefore, the findings of this study are expected to also have an impact on clinical practice and on the extension of treatment options for relevant mental disorders such as anxiety and depressive disorders.

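### The only power figure behind N = 70 comes from another trial's four-time-point comparison, at an α printed as 0.5, and does not carry over to this trial's primary analysis

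*Protocol article*

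**What the plan says.** The Sample size section gives three reasons for 35 patients per arm.

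- N = 70 lies within the range of sample sizes in a review of 19 studies of adjunctive apps. The section treats this as a firm basis for comparing efficacy.
- A second trial is cited as "a study employing a comparable methodology, which involves a comparison of two groups of 35 participants over four evaluation periods", among them pre-treatment and follow-up assessments. It expects moderate effects on homework adherence. Its power analysis, for a group comparison across four time points, is reported as "a power of 0.84 with a sample size of 35 per group (app vs. no app) at an α level of 0.5".
- Many observations per participant can raise power. THA will be rated for at least three tasks a week over about 16 weeks. The gain is not quantified.

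The section gives no numeric effect size, standard deviation, within-patient correlation, sidedness or attrition allowance, and no power figure for this trial's own analysis.

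Under Analyses of primary endpoint: "The primary endpoint is the overall THA score across the intervention", covering sessions 1–16. The model has the factor Group, "the within-subjects factor Time (T2, T3" as its only two levels, and their interaction. Under Missing data, multiple imputation is to "evaluate the potential impact of up to 20% attrition". The Discussion adds: "It is possible that a larger sample will be required to detect significant differences".

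**The concern.** The one number that could tell a reader how well N = 70 serves the primary question was computed for a different trial and a different analysis. That analysis had four time points, including one before treatment. The primary model here has two time levels, both after treatment has begun, and the endpoint itself is a single score per patient. The number of time points and the correlation between them drive the power of a repeated-measures group comparison, so the two designs are not comparable on the feature that matters. The printed α is not a usable test level either.

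A reader may carry 0.84 over to this trial and then take a null result as evidence that the app does not improve adherence, although the test may have had much less power than that. Falling within the range of published sample sizes does not help, because that range says nothing about power.

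**Working it through.** **Inputs from the protocol article.** 35 per arm, N = 70; other trial's power 0.84, four time points, α printed as 0.5 (Sample size). One overall score, Time at two levels (Analyses of primary endpoint). Attrition up to 20% (Missing data); 35 × 0.8 = 28 per arm if only completers count.

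**Assumptions, because the document gives no values.** Moderate means d = 0.5, that is f = d/2 = 0.25. The test is two-sided at α = 0.05. The correlation r between time points is equal for all pairs and is shown as a range.

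**1. Can the stated 0.84 be reproduced?** Not from the article's own inputs, since the effect size and correlation are missing. Two trials of it under the assumptions:

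- α = 0.5 as printed, one score, d = 0.5, 35 per arm: two-sided power 0.92. Power of 0.84 would need d of about 0.39.
- α = 0.05, between-group test averaged over m time points, noncentral F on 1 and N − 2 degrees of freedom with λ = f²·N·m / (1 + (m − 1)r). With m = 4 and r = 0.316: λ = 0.0625 × 70 × 4 / (1 + 3 × 0.316) = 17.5 / 1.948 = 8.98, power 0.84.

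So 0.84 is compatible with α = 0.05, a moderate effect, four time points and r of about 0.32. This suggests that 0.5 is a misprint.

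**2. One overall score per patient.** Noncentral t with δ = d·√(n/2).

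- n = 35: δ = 0.5 × √17.5 = 2.09, 68 df, power 0.541.
- n = 28: δ = 0.5 × √14 = 1.87, 54 df, power 0.451.
- Detectable d at 80% power: 0.68 (n = 35) and 0.76 (n = 28). Power of 0.84 with n = 35 needs d of about 0.72.

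**3. Two phase scores, d = 0.5 at each, Group effect averaged over T2 and T3 (m = 2).**

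| r | λ (N = 70) | Power, 35/arm | Power, 28/arm |
|---|---|---|---|
| 0.2 | 8.75/1.2 = 7.29 | 0.76 | 0.66 |
| 0.3 | 8.75/1.3 = 6.73 | 0.72 | 0.63 |
| 0.5 | 8.75/1.5 = 5.83 | 0.66 | 0.56 |
| 0.7 | 8.75/1.7 = 5.15 | 0.61 | 0.51 |
| 0.9 | 8.75/1.9 = 4.61 | 0.56 | 0.47 |

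At r = 0.316, where four points give 0.84, two points give 0.72 (0.62 with 28 per arm). With 35 per arm, two points reach 80% only if r is below about 0.08.

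**4. Effect defined per session.** If d = 0.5 applies to each of 15 rated sessions and these are averaged, the effect on the average is 0.5·√(15/(1 + 14r)).

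| r | d on the average | Power, 35/arm | Power, 28/arm |
|---|---|---|---|
| 0.3 | 0.85 | 0.94 | 0.88 |
| 0.5 | 0.68 | 0.81 | 0.71 |
| 0.7 | 0.59 | 0.68 | 0.58 |

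The Group × Time test cannot be evaluated, because no interaction effect is stated.

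**The case against.** The strongest objection is that the article never says its own power is 0.84. It attributes the figure to the other trial and names that trial's four time points. This stands: a reader might infer that the trial claims 84% power outright, and the text does not support that. The figure is nevertheless the only power the section offers for N = 70, so it serves as the justification.

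A reader might also infer that this design has 54% power, or 45% after attrition. The document does not support that either. Both figures depend on an effect size, sidedness and test level it does not state, and on defining d on the single overall score. The named model with two time levels gives higher figures, and a per-session definition gives up to 94% in the scenarios above. The article's remark about many observations per participant points that way, but it fixes neither the correlation nor the score to which the moderate effect applies. If the effect is defined on the overall score, the averaging is already included.

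The 28 per arm is a worst case. The 20% is an upper bound for a missing-data assessment, not a forecast. The primary set is intention-to-treat, multiple imputation is planned, and data collected before discontinuation are used.

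Finally, the Discussion concedes that a larger sample may be needed, which lowers the risk of misreading a null result. It neither corrects α nor supplies the missing figure.

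**Conclusion.** The point holds in this form: the printed α is wrong, and the borrowed 0.84 does not describe this trial's primary analysis, which has one overall score, two time levels and no stated attrition allowance in the sample size. For d = 0.5 and two-sided α = 0.05, power with 35 per arm is about 54% if d refers to the overall score and about 76% to 56% for two phase scores correlated 0.2 to 0.9. The worst case of 28 completers per arm gives about 45% and 66% to 47%. The detectable d at 80% power on one score is about 0.68, or 0.76 with 28 per arm. These are conditional illustrations, not the trial's own figures. A per-session effect with modest correlation could bring power above 80%, but the document does not say that this is what is meant.

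**What to change.** In the Sample size section:

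- Correct α, or explain it if 0.5 was intended.
- Label 0.84 as the other trial's figure and do not use it as the power of this trial.
- State the power or the detectable effect for this trial's own primary Group comparison. Give the test level and sidedness, the effect size and the score it is defined on (overall, phase or session), the within-patient correlation, and the attrition assumed. If the sponsor adopts the assumptions used here, the figures above can be entered; otherwise it should supply its own.
- Remove the inference that lying within the range of published sample sizes is a firm basis for the comparison.

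The cost is rewording one section and, under the overall-score and two-phase scenarios, a less favourable stated power. No extra patients and no change in conduct are needed.
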